#### Tumor Imaging

Tumor imaging may include CT/PET-CT scans and/or MRI. These will complement physical exam and other imaging as required, but the primary assessments will be based on CT/PET-CT and/or MRI. For each participant, the same method of assessment should be used at baseline and throughout the course of the study.

#### Tumor Measurements

Patients enrolled on this trial are not expected to have measurable disease.

### **6.9.2 Immunologic Assessments**

Assessments of T cell function may include, but are not limited to the following:

- ELISpot assays
- ELISAs
- Chromium-release assays
- Proliferation assays
- Intracellular cytokine staining
- T cell receptor sequencing.
- Cytokine bead array
- Flow cytometry
- HLA typing

Characterization of cellular populations may include, but are not limited to the following:

- Immunohistochemistry
- Gene expression analysis
- Flow cytometry
- ELISAs

- Western-blot analysis
- Intracellular cytokine staining
- Cytokine bead array
- T cell receptor analysis

## 6.10 **Study Calendar**

See [Section 9.1](#).

## 7.0 **STATISTICAL CONSIDERATIONS**

This is an early phase randomized trial to obtain preliminary data on the safety and immunogenicity of CDX-1127 (CD27 antibody) administered concurrently with a melanoma vaccine (6MHP). The primary goals are to assess the safety of CDX-1127 when administered with vaccine; and to obtain preliminary estimates of the difference in immune outcome measures between participants randomized to 6MHP + CDX-1127 (Arm A) versus 6MHP (Arm B). Exploratory goals are to obtain preliminary data on the induction of antibodies; CD8+ T cell response to antigens; cell activation and exhaustion; and clinical outcomes. Eligible participants will be accrued and randomized with equal allocation to one of two treatment arms as shown in [Table 9](#).

**Table 9: Arms**

|                                                                    |
|--------------------------------------------------------------------|
| A: 6MHP + Montanide ISA-51 + polyICLC + CDX-1127 (6MHP + CDX-1127) |
| B: 6MHP + Montanide ISA-51 + polyICLC (6MHP)                       |

## 7.1 **Evaluation of Sample Populations and Endpoints**

### 7.1.1 **Safety**

All participants receiving any protocol defined treatment will be evaluated for safety.

The 6MHP vaccine has been safe, with lower toxicities than with class I peptides, in particular with lower autoimmune or hyperimmune toxicities. Data from MEL63 indicates a DLT rate of 6.3% with a 95% CI(1, 18%). Reported DLT information (ref: Burris et al JCO May 2) for CDX-1127 in patients with advanced solid tumors indicated a DLT rate of 4% with a 95% CI(<1, 20%). We do not anticipate increased toxicities by combining 6MHP vaccine with CDX-1127 therefore, this trial will be designed with stopping rules for DLT rates beyond those expected with vaccine alone or CDX-1127 alone. Formal safety bounds based upon monitoring dose limiting toxicities (DLT) ([Section 8.9](#)) will guide decisions about early stopping due to potential safety concerns. If a stopping bound is crossed then accrual to the study will be suspended until the study PI, co-investigators and the DSMC can review the data, and determine if the study should continue, be amended or be closed to further accrual.

### 7.1.2 **Immunogenicity**

All eligible participants receiving any protocol defined treatment who have at least two evaluable blood draws (including baseline) for immune analyses will be evaluated for the following immune response parameters. In addition, all

participants are considered 'evaluable' for the primary endpoint if they have been evaluated for immune response at baseline and at least day 127; or they have progressed prior to the day 127 assessment; or have stopped treatment due to DLTs.

In PBMC:

- CD4+ Th1 response to vaccine antigens by ELIspot:
  - Magnitude of response at all times
  - Frequency of response over time
  - Persistence of response over time
- Circulating regulatory T cells (Tregs) as measured by flow cytometry over time
- CD8+ T cell responses to peptides not in the vaccine over time
- CD4+ T cell activation versus exhaustion
  - Activation measured by an increase in %DR+ CD4+ cells of total CD4+ cells
  - Exhaustion measured by increase in the % of DR+CD4+ T cells that co-express both PD-1 and either LAG3 or TIM3.

In the tumor microenvironment:

- FoxP3+ CD4+ T cells per mm^2 in vaccine site biopsies by immunohistochemistry and gene expression analysis at weeks 3 and 12. **Note:** with revision to reduce ulceration at vaccine sites, biopsies are not required at week 12 for participants whose week 12 visit would be due after IRB approval of Protocol v12-03-2020.

In serum:

- IgG antibodies to 6MHP by ELISA for IgG over time

A CD4+ T cell response to 6MHP (Rsp), is defined as all of the following, based on direct ELIspot assay:

- a) an increase of at least 20 IFN-gamma secreting cells per 100,000 CD4+ T cells, over the maximum of the negative controls ( $T_{\text{neg cctrl}}$ )
- b) no overlap in standard deviations between the response to 6MHP peptide pool ( $T_{\text{vax}}$ ) and  $T_{\text{neg cctrl}}$
- c) the ratio of  $T_{\text{vax}}$  to  $T_{\text{neg cctrl}}$  at one or more time points, after week 0, is at least 5-fold the prevaccine ratio of  $T_{\text{vax}}$  to  $T_{\text{neg cctrl}}$ . Note that any prevaccine ratio of  $T_{\text{vax}}$  to  $T_{\text{neg cctrl}}$  below 1 will be set to 1 to avoid overinflating that ratio.

A durable response (dRsp) is defined as a Rsp detected over at least two consecutive time periods during vaccination (days 8 through 85).

A persistent response (pRsp) is defined as a dRsp plus a Rsp detected on day 127 or 176.

A memory recall (mRsp) is defined as a Rsp detected at any time point from day 8 through day 85, and a Rsp on day 183 compared to the Rsp on day 176, with all of the following:

- a) an increase of at least 20 IFN-gamma secreting cells per 100,000 CD4+ T cells over  $T_{\text{neg cctrl}}$  at day 183.
- b) no overlap in standard deviations between  $T_{\text{vax}}$  and  $T_{\text{neg cctrl}}$  at day 183.

- d) at least a 2-fold increase in the ratio of  $T_{\text{vax}}$  to  $T_{\text{neg cntrl}}$  compared to the ratio of  $T_{\text{vax}}$  to  $T_{\text{neg cntrl}}$  at day 176. Note that if that ratio at day 176 is below 1, it will be set to 1 to avoid overinflating response assessment at day 183.

Evaluable participants who have progressed prior to the day 127 assessment or have stopped treatment due to DLTs will be considered response failures for dRsp, pRsp and mRsp.

Measures of CD8+ T cell responses by ELISpot will use the same criteria defined above, except that that definition of response will be based on response to peptides restricted by Class I MHC molecules, and the data will be normalized to the number of CD8+ T cells in the assays (eg: criterion of at least 20 IFN-gamma secreting cells per 100,000 CD8+ T cells over  $T_{\text{neg cntrl}}$ ).

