## 5.6 Discontinuation of Therapy

Protocol treatment will be discontinued for any of the following reasons:

- Any dose-limiting toxicity as defined in [Section 8.9](#).
- Disease progression requiring other therapy (e.g. surgery under general anesthesia, radiation, chemotherapy, or steroid therapy). The appearance of small metastases or recurrent tumor deposits will not be a basis for discontinuing the study treatment. Biopsy to determine the nature of new lesions or minor surgical procedures to excise a new lesion (with or without anesthesia) will not be a basis for discontinuing study treatment.
- Initiation of cytotoxic chemotherapy, radiation therapy, surgery for resection of disease, steroid therapy, or other immunosuppressive therapy.
- Any other potential adverse reaction deemed sufficiently serious to warrant discontinuation of therapy by the Principal Investigator or one of the Associate Investigators.

- Noncompliance with the requirements of the study.
- Therapy may be discontinued at the participant's request.
- Therapy may be discontinued at the discretion of an Investigator.
- Pregnancy. Pregnant participants will continue to be followed for the duration of the pregnancy.

Participants who discontinue treatment will be followed according to the follow-up schedule outlined in [Section 9.1](#), unless a participant has withdrawn consent.

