## 7.2 Sample Size and Accrual

Target sample size was based on the number of participants that could be accrued within the funding amount. This was set at 30 evaluable participants.

A primary endpoint for this study is a persistent response (pRsp) to vaccine antigens (see section 7.1.2). Results from Mel63 for the 38 evaluable participants treated on Arms C & D (6MHP + Montanide ISA-51 + polyICLC without & with mCy) resulted in 5 participants with a pRsp (13.1%). The 90% CI for this estimate is (5.3% to 25.7%) resulting in a half-width of 10.2%. For this study, an observed difference in the persistent response rates in the range of 28% to 31% (approximately 3 times the half-width) is needed to support that the addition of CDX-1127 to 6MHP vaccine warrants further study. This determination is based upon having positive lower and upper 90% CI bounds for the difference in pRsp for study Arm B – Arm A assuming Arm A pRsp rates of 13.1% to 25.7% using the score method of Miettinen and Nurminen.

Maximum target sample size is estimated to be 34 participants, which assumes a 10% dropout/ineligibility/lost to follow-up adjustment. Accrual is estimated at approximately 20 participants per year, therefore, accrual to the study should be completed in two years with final analysis occurring 9-12 months later.

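### The primary evaluability rule requires day 127 although pRsp can be met on day 176, drops non-DLT early stoppers but keeps progression and DLT stops as failures, and overrides dRsp already observed

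*Combined protocol and SAP*

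**What the plan says.** **Evaluability.** Section 7.1.2 first describes a general immune-response set: eligible, treated, with at least two evaluable draws including baseline. It then adds a condition for the primary endpoint: the participant was "evaluated for immune response at baseline and at least day 127; or they have progressed prior to the day 127 assessment", or stopped treatment because of a DLT.

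**Endpoint.** The same section states: "A persistent response (pRsp) is defined as a dRsp plus a Rsp detected on day 127 or 176". The synopsis and Section 2.1 also allow either day, or both. dRsp needs a response at two or more consecutive time points within days 8 to 85.

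**Failure rule.** "Evaluable participants who have progressed prior to the day 127 assessment or have stopped treatment due to DLTs will be considered response failures". The rule covers durable, persistent and memory responses alike, with no exception for a response already observed.

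**Other routes off treatment.** Section 5.6 lists noncompliance, investigator discretion and adverse reactions other than DLTs, and adds: "Therapy may be discontinued at the participant's request". Note a to Table 7 adds repeated vaccine delays. Section 5.6 refers those who discontinue to the follow-up schedule in Section 9.1. There, research bloods are drawn only at EOT 1 and EOT 2 (7 days after stopping vaccine), followed by a 30-day contact and annual survival follow-up.

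**Benchmark.** Section 7.2 says that "an observed difference in the persistent response rates in the range of 28% to 31% (approximately 3 times the half-width) is needed" to support further study, based on "having positive lower and upper 90% CI bounds for the difference in pRsp for study Arm B – Arm A".

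**The concern.** Three rules in one section do not fit together.

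1. The endpoint can be met on day 176, but the evaluable set is closed to anyone without day 127 unless they progressed or had a DLT. A dRsp participant who misses or fails the day-127 assay and responds on day 176 meets the definition but is not counted.
2. Two kinds of early stopper are handled in opposite ways. Progression and DLT stops count as failures. Someone who stops all treatment early for another reason is not scheduled for day-127 blood and leaves the denominator. Section 3.3 says participants know their treatment, so such withdrawals can differ by arm, and the comparison is then no longer between the groups as randomised.
3. dRsp is settled by day 85. Progression on day 100, or a later DLT stop, cannot undo it, yet it is recoded as failure. Section 7.5 plans a 90% CI for the dRsp difference, so a named analysis is affected.

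The trial plans about 15 per arm, and one participant is 1/15 = 6.7 percentage points.

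**Working it through.** **Inputs.** From Section 7.2: 5/38 with pRsp in Mel63 Arms C and D, 30 evaluable, up to 34 accrued with 10% loss, and the 90% Miettinen-Nurminen score interval. From the synopsis: 15 per arm. Section 7.2 writes the difference as Arm B minus Arm A with Arm A as control, while Table 9 gives CDX-1127 to Arm A. All differences below are CDX-1127 minus vaccine alone, with the CDX-1127 arm first.

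**The plan's own figures.**
- The exact (Clopper-Pearson) 90% CI for 5/38 is 5.3% to 25.7%, half-width 10.2%. This matches Section 7.2.
- With 15 per arm, the lower bound reaches zero at a difference of 27.0% (control 13.1%) and 30.0% (control 25.7%). The stated 28% to 31% agrees within one point.
- 30/0.9 = 33.3, rounded up to 34. This matches.

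**Formula.** The lower 90% bound is above zero when z = d / √[p(1−p)(1/n₁+1/n₂)·N/(N−1)] exceeds 1.645, where d is the observed difference, p the pooled proportion and N = n₁+n₂.

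**Unequal loss, one non-responder without day 127.**
- 6/15 v 2/15: d = 0.2667, p = 8/30, standard error √[0.1956 × 0.1333 × 30/29] = 0.1642, z = 1.624. CI -0.4% to 50.9%: benchmark not met.
- 6/14 v 2/15: d = 0.2952, p = 8/29, standard error √[0.1998 × 0.1381 × 29/28] = 0.1690, z = 1.747. CI +1.8% to 54.2%: met.
- 7/15 v 3/15 has lower bound -2.2%; 7/14 v 3/15 has +0.4%.
- Loss from the control arm can act in the other direction: 10/15 v 5/15 has +2.8%; 10/15 v 5/14 has -0.1%.

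**Balanced loss.**
- 6/14 v 2/14: z = 1.643, lower bound -0.03%. Not met, as with 6/15 v 2/15.
- 17 treated per arm against 15 evaluable per arm: 6/17 v 2/17 (-0.8%) and 6/15 v 2/15 (-0.4%) both miss. 7/17 v 2/17 (+4.4%) and 7/15 v 2/15 (+5.6%) both meet.

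**How often the two denominators disagree.** This is exact binomial enumeration, comparing exclusion with counting the same people as failures. The documents do not give the number lacking day 127, so the patterns are assumptions within the 10% allowance.

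| Assumed loss (CDX-1127 arm, control arm) | True rates 13.1% v 41.1% | True rates 25.7% v 56.7% |
|---|---|---|
| 1 of 15, 0 of 15 | 9.3% | 7.3% |
| 0 of 15, 1 of 15 | 0.1% | 3.2% |
| 3 of 17, 1 of 17 | 10.6% | 15.2% |
| 1 of 17, 3 of 17 | 7.9% | 12.7% |
| 2 of 17, 2 of 17 | 0.0% | 0.0% |

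In the first row the chance of meeting the benchmark is 55.4% with exclusion and 46.1% counting the participant as a failure (13.1% v 41.1%), or 51.9% and 44.6% (25.7% v 56.7%).

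**dRsp.** The Section 9.1 calendars schedule research bloods on days 15, 22, 36, 57, 78 and 85, so dRsp can be fully classified before day 127. To show scale only: if 7/15 v 2/15 had dRsp and one CDX-1127 responder were recoded, the difference would fall from 33.3% (lower bound +5.6%) to 26.7% (-0.4%).

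**The case against.** **The crossing is a narrow case.** It needs borderline counts and unequal loss. With 2 to 5 control responders and 15 per arm, dropping one CDX-1127 non-responder changes the outcome only at 6 v 2 and 7 v 3. A reader might infer that any single exclusion reverses the conclusion; the calculations do not support that. This stands as a limit on size.

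**It is not a formal decision.** Section 7.5 describes an estimation study without statistical comparison of arms, and 26.7% and 29.5% are nearly the same estimate with wide intervals. This also stands. The benchmark is nevertheless the plan's only stated criterion for further study.

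**Missing day 127 should be uncommon in those still attending.** Table 7 keeps the day-127 labs open even at 15 or more days off schedule. That reduces the problem, but failed assays and early stoppers remain.

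**The wider two-draw set already covers persistence.** It does list persistence over time, but the words linking it to the primary set leave their relation unclear. Neither set counts missing samples as failure.

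**The failure rule is a pre-specified composite.** For pRsp this is a defensible, conservative choice, and I would not remove it. The argument does not carry over to dRsp, which is complete before the events that override it may occur.

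**DLT counts.** A reader might infer from Section 1.1 (three ulceration DLTs and a grade 3 pneumonitis) that about four of the first 15 participants had responses overwritten. Section 1.1 gives no denominator, does not say that the events were in different participants, and does not say that any of them had reached dRsp.

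**Conclusion.** The point holds as an inconsistency in the analysis rules that should be corrected. As written, Section 7.1.2 excludes participants who can meet the endpoint on day 176, treats early stoppers differently by reason for stopping, and reclassifies durable responses already observed.

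The numerical effect is conditional. One unmatched exclusion can move a borderline result across the benchmark (lower bound -0.4% to +1.8% at 6 v 2). Under the loss patterns assumed above, the two denominators disagree in 0% to about 15% of trials. Equal loss changed no outcome in the tables checked. These figures assume true rates at the plan's own benchmark and treat missing participants as non-responders. The number actually lacking day 127, and the number of dRsp results overridden, cannot be known from the documents. The documents do not show that the trial's conclusion was altered, nor that the progression/DLT failure rule is wrong for pRsp.

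**What to change.** Revise Sections 7.1.2 and 7.5 as follows:

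- Analyse pRsp in all eligible participants who received any protocol treatment, by assigned arm.
- Let a sample on day 127 or day 176 suffice. Count participants with neither as non-responders, whatever the reason.
- Keep the pre-specified failure rule for pRsp (progression before day 127, or a DLT stop).
- Assess dRsp on the observed samples from days 8 to 85, and impute failure only where too few exist to classify it.
- Report the current evaluable set as a sensitivity analysis, with the number and reason for each exclusion by arm.

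No new data or visits are needed. The costs are slightly lower estimated response rates, and a denominator that differs somewhat from the Mel63 evaluable set used to derive the 28% to 31% benchmark. The sensitivity analysis preserves that link.

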### 7.5 **Analyses**

Study populations and evaluation criteria are noted in [Section 7.1](#). Adverse events will be summarized by frequency and magnitude of event. Incidence of DLTs will be monitored against the safety bounds above. The bounds are non-binding, and provide a guideline that may result in study modification or closure.

A 5-fold or greater CD4+ Th1 memory response to vaccine antigens compared to baseline is consider a response. Amounts less than 5-fold are considered as a non-response. Immune and clinical endpoints are defined in [Section 7.1.2](#) and in [Section 7.1.3](#), respectively. Time to event measures (DFS and OS) will be estimated by the methods of Kaplan and Meier.

This study is designed to estimate differences and not to make statistical comparisons between arms. All CD4+ T cell and CD8+ T cell ELISpot results will be assessed relative to the participant specific baseline measure with graphical representation of measures over time. The difference in the proportion of participants considered to have a durable response between arms will be estimated and a 90% confidence interval around the difference, using the score method of Miettinen and Nurminen. Similarly, the difference in

the proportion of participants considered to have a memory response at day 183 between arms will be estimated and a 90% confidence interval around the difference calculated. In addition, repeated measure models will be explored to estimate difference in patterns of response between arms over time for CD4+ T cell, CD8+ T cell and percent of circulating Tregs (with a log10 transformation). Within an arm, for each participant, the difference in amount of FoxP3+ cells in the vaccine site microenvironment at weeks 3 and 12 (for those with biopsies done on week 12) will be calculated. Estimated difference in mean change by arm with 90% CI estimates around the difference in means will be used to estimate potential differences by arm.

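### The 5-fold criterion in the response definition is not tied to the visit being scored, so read literally an early peak lets a late value near baseline count as persistent

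*Combined protocol and SAP*

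**What the plan says.** Section 7.1.2 (Immunogenicity) defines a response (Rsp) to the 6MHP pool by three criteria, all of which are required:

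- (a) "an increase of at least 20 IFN-gamma secreting cells per 100,000" CD4+ T cells over the highest negative control;
- (b) "no overlap in standard deviations between the response to 6MHP peptide pool" and the negative control;
- (c) a ratio of pool to negative control that, "at one or more time points, after week 0, is at least 5-fold the prevaccine ratio". A prevaccine ratio "below 1 will be set to 1 to avoid overinflating that ratio".

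The composite endpoints reuse Rsp at particular times. The first is worded as follows: "A durable response (dRsp) is defined as a Rsp detected over at least two consecutive time periods during vaccination (days 8 through 85"). The next one, abbreviated pRsp, builds on it and is the primary immunogenicity endpoint in Section 2.1: "A persistent response (pRsp) is defined as a dRsp plus a Rsp detected on day 127 or 176".

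The memory response (mRsp) has its own late criteria in Section 7.1.2. These name day 183 and use day 176 as the comparator for a 2-fold rise.

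Section 7.5 adds: "A 5-fold or greater CD4+ Th1 memory response to vaccine antigens compared to baseline is consider a response". It classes anything below 5-fold as a non-response, and says that all ELISpot results are assessed against the participant's own baseline.

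**The concern.** Criteria (a) and (b) compare the vaccine pool with the negative control. Only (c) measures change from before vaccination, and its wording suits a participant-level question: did this person ever reach 5-fold? That fits secondary objective 2b, which concerns the response at any time point. It does not fit a definition that is then applied visit by visit for the durable response (dRsp) and pRsp.

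Taken as written, a participant who reaches 5-fold once has met (c) for good. A later visit then needs only (a) and (b), which pre-existing reactivity or a high negative control can supply. The primary endpoint is meant to show that a vaccine-induced rise has lasted. Under this reading it can be met by a transient rise on top of reactivity that was there before treatment. Two analysts following the text could score the same participant differently, and with 15 participants per arm one score can matter.

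**Working it through.** **1. The plan's own figures (Section 7.2).** The Mel63 rate is 5/38 = 13.2% (printed as 13.1%). The exact (Clopper-Pearson) 90% interval is 5.3% to 25.7%, with half-width (25.7 − 5.3)/2 = 10.2. Both agree with the plan. With 15 per arm, the Miettinen-Nurminen 90% lower bound reaches zero at a difference of 27.0 points for a control rate of 13.1%, and at 30.0 points for 25.7%. This agrees with the stated 28% to 31% to within about one point. None of these calculations depends on how (c) is read.

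**2. The two readings applied to one profile.** The plan gives no participant-level ELISpot counts, so these values are assumed (per 100,000 CD4+ cells), and (b) is taken as met. Days 36 and 57 are adjacent research-blood visits in the Section 9.1 calendars. Excess = pool − control. Ratio = pool/control. Fold = ratio/prevaccine ratio.

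| Visit | Pool | Control | Excess | Ratio | Fold | Rsp, (c) met at any visit | Rsp, (c) at this visit |
|---|---|---|---|---|---|---|---|
| Baseline | 40 | 15 | 25 | 2.67 | – | – | – |
| Day 36 | 220 | 15 | 205 | 14.67 | 5.5 | yes | yes |
| Day 57 | 42 | 15 | 27 | 2.80 | 1.05 | yes | no |
| Day 127 | 42 | 15 | 27 | 2.80 | 1.05 | yes | no |

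Read literally, days 36 and 57 give a dRsp and day 127 completes a pRsp. With (c) applied at each visit, only day 36 is a response, so there is neither a dRsp nor a pRsp.

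**3. How far this extends.** Further assumed profiles, as pool/control:

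| Baseline | Peak | Day 127 | Late excess | Late fold | Late Rsp, literal | Late Rsp, same visit |
|---|---|---|---|---|---|---|
| 30/6 | 160/6 (5.3-fold) | 30/6 | 24 | 1.0 | yes | no |
| 10/10 | 100/10 (10-fold) | 30/10 | 20 | 3.0 | yes | no |
| 10/10 | 100/10 (10-fold) | 60/40 | 20 | 1.5 | yes | no |
| 10/10 | 100/10 (10-fold) | 12/10 | 2 | 1.2 | no | no |

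The last row shows that a fall to background fails (a) under either reading, provided (a) is applied on that day.

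With a baseline ratio of 1 or less (set to 1), the fold at the (a) threshold is (control + 20)/control. That is at least 5 only when the control is 5 or lower. It falls to 3.0 at a control of 10, 2.0 at 20 and 1.5 at 40. So (a) stands in for (c) only when the background is very low.

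**4. What one participant is worth.** One of 15 is 1/15 = 6.7 points. With equal arms of 15 the difference moves in steps of 6.7 points: 4/15 = 26.7 falls short of the stated hurdle, and 5/15 = 33.3 is the first step that clears it. Section 7.2 requires a 90% interval that lies above zero. The Miettinen-Nurminen lower bounds are:

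| Higher arm | Lower arm | Difference | Lower bound |
|---|---|---|---|
| 7/15 | 2/15 | 33.3 points | +5.6% |
| 6/15 | 2/15 | 26.7 points | −0.4% |
| 7/15 | 3/15 | 26.7 points | −2.2% |

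Removing one responder from the higher arm, or adding one to the lower arm, changes the conclusion.

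**The case against.** The strongest reply is that per-visit scoring is already the natural reading. A dRsp requires responses over consecutive periods and a pRsp requires one detected on a named day. If a response means that all three criteria hold, a response on day 127 should mean that all three hold on day 127. Criteria (a) and (b) name no day either, so it is selective to apply those two on the late visit while treating (c) as carried forward. Section 7.5 points the same way, through its baseline comparison for all ELISpot results and its rule that less than 5-fold is a non-response.

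Much of this stands. It shows what was probably meant, and it rules out treating the literal reading as the settled scoring rule. It does not repair the definition: (c) says in terms that one time point is enough, and the 5-fold sentence in Section 7.5 is worded for the memory response and names no visit for pRsp.

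It is also fair that the profiles above are hypothetical, and that near-baseline persistence needs pre-existing reactivity or a high negative control. A reader might infer that a response which has disappeared can count as persistent. The documents do not support that if (a) is applied on the late day. Nor do they support extending the point to the late part of mRsp, which has its own day-183 criteria.

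**Conclusion.** The point holds as a conflict between the operative wording and the evident intent, in the definition of the primary immunogenicity endpoint. Followed literally, (c) allows a late ratio at or near baseline to count toward dRsp and pRsp. The rest of the plan suggests that this was not meant. It should be corrected before response is scored.

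The size is bounded only per participant: 6.7 points of an arm's rate for each one affected, with one enough to reverse the decision in the scenario of 7/15 against 2/15. That rests on 15 evaluable participants per arm and on the Section 7.2 rule. How many participants are affected cannot be computed from the documents.

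A reader might also infer that pRsp will be inflated, that a CDX-1127 effect will be diluted, or that the Mel63 rate of 5/38 was scored differently. None of these can be established. The documents available do not show which reading will be used or which one produced 5/38, and they give no basis for a direction of bias between arms. The Mel63 question is something to check, not a finding.

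**What to change.** In Section 7.1.2, state that (a), (b) and (c) must all be met at the same time point for a Rsp at that time point. Reword (c) so that the ratio at that time point is at least 5 times the prevaccine ratio. Define the overall response for objective 2b separately, as a Rsp at one or more time points. Bring the 5-fold sentence in Section 7.5 into line, and leave the day-183 criteria for mRsp as they are. Check that the Mel63 5/38 was scored by the same rule. If it was not, re-score it and revisit the Section 7.2 hurdle.

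The cost is a few sentences and a re-derivation from existing ELISpot data, with no new samples. If per-visit scoring is already the practice, no result changes. Otherwise dRsp and pRsp rates may fall slightly in both arms.
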